#### Teachers

For the first 4 research stages (IDENTIFY, DEFINE, POSITION, and CONCEPT), we will recruit approximately 24 high-school teachers. Within this sample, we will purposefully sample those teachers who will be involved in later stages of the delivery of the intervention. Specific attention will also be paid to involve physical education teachers. Within the CREATE research stage, we will sample 15 teachers to participate in the pilot study, representing 2 different schools. Finally, for the final research stage (USE) 50 teachers will be recruited from different schools to participate in the educational module for teachers.

#### Parents

For the first 4 research stages (IDENTIFY, DEFINE, POSITION, and CONCEPT) we will recruit approximately 24 parents of children enrolled within the Brussels school context. Within this sample, we will strive for a relatively heterogeneous group, recruiting parents of children from different schools, different education levels, different ethnic backgrounds, and with a balanced gender distribution. Within the CREATE research stage, we will sample 15 parents to participate in the pilot study, representing parents of pupils from 2 different schools. Finally, for the final research stage (USE) 50 parents will be recruited from different schools to participate in the educational module for parents.

#### Experts

For the IDENTIFY, POSITION, and CONCEPT research stages, an interdisciplinary group of applied and academic experts will be involved to help shape the evidence-informed intervention. We expect approximately 16 experts to be involved within the project’s life span. These experts will be recruited based on their specific expertise and applied experience within the project topic and setting and through the different project partners. These experts will consist of the following:

4 school directors and 4 “zorgcoördinators” (care coordinators) from different schools within the Brussels region;2 school counseling consultants from different schools within the Brussels region;2 government prevention advisors with specific expertise in mental health and well-being;4 academic experts with specific expertise in mental health and well-being and (clinical) sport psychology.

### Procedures

Based on the project design outlined above (see Table 1), 4 main work packages are proposed. Each of the work packages is described separately below.

#### Work Package 1

The first work package will encompass the IDENTIFY and DEFINE research stages. Key activities and milestones within this work package include the following:

Focus group interviews with pupils, teachers, and parents: focus groups will be conducted to (1) understand the problem from the perspective of the end users and (2) help define objectives to address this given problem.Consultations with experts: consultations will be conducted to understand the problem from the perspective of applied and academic experts.Scoping review of the literature: a scoping review will be conducted to (1) evaluate epidemiological evidence and (2) identify risk factors and resources for adolescent mental health.

#### Work Package 2

The second work package will encompass the POSITION and CONCEPT research stages. Key activities and milestones within this work package include the following:

Co-design workshops with pupils, teachers, and parents: co-design workshops will be conducted to understand how the intervention needs to be positioned from the perspective of the end user and generate intervention content.Review of behavior change theories: a brief literature review will be conducted on leading behavior change theories that can aid in the design of engaging, evidence-informed intervention content.Consultations with experts: consultations with experts will be conducted to establish key indicators to evaluate the intervention process, impact, and outcome based on content developed during the co-design workshops.

#### Work Package 3

The third work package will encompass the CREATE research stage. Key activities and milestones within this work package include the following:

Pilot study with detailed process evaluation by intervention end users; a detailed pilot study will be conducted to test the intervention with a small sample of end users.Build, test, and finalize data collection battery (quantitative and qualitative); a battery will be developed and tested during the pilot study based on the established indicators for intervention process, impact, and outcome (see WP 4).

#### Work Package 4

The fourth work package will encompass the USE research stage. Key activities and milestones within this work package include the following:

Implementation of a group-controlled quasi-experimental intervention: a quasi-experimental intervention will be conducted, randomly allocating participants at group level (ie, class) to either experimental or control conditions. The experimental condition will receive the intervention over a 6-month period, whereas the control group will serve as a “usual care” control group. Additionally, a selected sample of teachers and parents of pupils within the experimental group will be provided with the complementary educational modules.Pretest, posttest, and 3-month follow-up (quantitative and qualitative) evaluations; a 3-wave data collection design will be adopted to collect both qualitative and quantitative data on the intervention process, impact, and outcome. These include pretest, posttest, and 3-month follow-up data collection points.

### Data Collection

Throughout the project, a mixed methods approach to data collection will be adopted. Qualitative data will be collected primarily through focus group interviews and co-design workshops. Each focus group and co-design workshop will be both audio- and video-recorded. Audio recordings will be transcribed verbatim, and transcriptions will be used for further analysis. Video recordings can be used to clarify the context of certain statements or to ascertain group dynamics within the interviews or workshops that cannot be discerned through audio alone.

Quantitative data will also be collected to evaluate program outcomes during the CREATE and USE research stages. In line with our participatory design approach, the determination of the most relevant project outcomes and the development of a corresponding test battery to assess these outcomes will be based on a co-design process during the project life span. As such, we have purposefully not determined an a priori set of outcome measures. However, an indicative set of outcome measures includes the following:

subjective well-being, as measured using the World Health Organization-Five Well-Being Index (WHO-5) [46];psychological distress, as assessed using the Kessler Psychological Distress Scale [47];mental health stigma, as assessed using the Peer Mental Health Stigma Scale [48];help-seeking intentions, as measured by the ﻿Attitudes Toward Seeking Professional Psychological Help Scale-Short Form [49]; andemotion regulations, as measured by the ﻿Difficulties in Emotion Regulation Scale [50].

### Data Analysis

Qualitative data will primarily be analyzed using reflexive thematic analysis. Reflexive thematic analysis is particularly suited to gain sense and meaning from participants’ lived experiences while at the same time recognizing the subjectivity of human experience and emphasizing that meaning-making from this experience is the result of a process of cocreation between the participant and the researcher [51]. To support our co-design principles and involve participants as active contributors throughout all phases of the analysis process, member reflections will also be used. Member reflections are structured opportunities for participants to provide feedback and reflection on tentative qualitative analysis, not as a way to verify the truthfulness of the analysis but rather as a way to generate novel insights and data [52].

Within the USE research stage, analysis of the main outcome measures will be calculated using a mixed-model ANOVA including 2 groups (mental health program vs control group) and measures at 3 time points (pre, post, and 3-month follow-up). Missing data will be dealt with by using appropriate methods.

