### Participants

#### Pupils

For the first 4 research stages (IDENTIFY, DEFINE, POSITION, and CONCEPT) we will recruit approximately 60 high-school pupils enrolled within the Brussels school context (aged 12-15 years). Within this sample, we will strive for a relatively heterogeneous group, recruiting participants from different schools, different education levels, different ethnic backgrounds, and with a balanced gender distribution. Within the CREATE research stage, we will sample an additional 40 pupils, representing 2 different classes. These classes will be purposefully selected from different schools to complete a pilot study of the proposed intervention. Finally, for the final research stage (USE), 300 participants will be recruited to complete the intervention, with another 300 pupils acting as matched controls. Pupils will be recruited from different schools, different educational levels, and different ethnic and socioeconomic backgrounds. The total number of participants within the USE phase is sufficient to ensure enough power for the planned statistical analyses and takes into account an attrition rate of 30%.

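### Classes are randomised, but the stated ANOVA has only group and time terms, so it treats pupils as independent and overstates significance

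*Protocol article*

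**What the plan says.** Under Procedures, Work Package 4, the USE stage is a controlled comparison "randomly allocating participants at group level (ie, class) to either experimental or control conditions". The intervention arm receives the programme over 6 months and the other arm receives usual care.

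Under Participants, Pupils, "300 participants will be recruited to complete the intervention, with another 300 pupils acting as matched controls". This total is described as "sufficient to ensure enough power for the planned statistical analyses and takes into account an attrition rate of 30"%.

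Under Data Analysis, "analysis of the main outcome measures will be calculated using a mixed-model ANOVA including 2 groups (mental health program vs control group"). The second factor is time, with three levels: before the programme, after it, and 3 months later. The only further sentence on the quantitative analysis concerns missing data. The article nowhere mentions a class or school effect, an intraclass correlation (ICC), a design effect or the number of classes in the USE stage.

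**The concern.** A mixed-model ANOVA with one between-subject factor (group) and one within-subject factor (time) is the usual name for a split-plot analysis with the pupil as the subject. It allows for correlation between a pupil's three measurements. It assumes that different pupils are independent.

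Allocation by class breaks that assumption. Pupils in one class share teachers, peers and events, and those in the programme arm also share the sessions. Candidate outcomes such as peer stigma and help-seeking are likely to move together within a class. If the model ignores this, standard errors are too small, confidence intervals too narrow and p-values too low. A few classes with a good teacher or a bad term can then pass for a programme effect. This matters here because the Introduction itself warns that universal school programmes may be ineffective or even harmful.

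**Working it through.** **The plan's own figure.** The 600 pupils cannot be reproduced, because the article gives no effect size, power, significance level or ICC. Only the attrition arithmetic can be followed: 300 × 0.70 = 210 completers per arm, 420 in total.

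**Inputs**
- Class size: about 20, from the pilot stage ("we will sample an additional 40 pupils, representing 2 different classes"). Carrying this over to the USE stage is an assumption.
- Classes: 300 / 20 = 15 per arm, 30 in total.
- Completers per class: m = 20 × 0.70 = 14.
- Total variance is set to 1. Half is stable within a pupil (within-pupil correlation 0.5, assumed). The class-by-time share is c and the residual is 0.5 − c. The article does not give c, so a range is shown.

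**Group-by-time test.** With no programme effect, the group-by-time mean square has expectation (0.5 − c) + m·c. The pupil-level error mean square has expectation of about (0.5 − c) + c = 0.5. The F statistic is therefore inflated by

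R = (0.5 − c + 14c) / 0.5.

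With 2 numerator and many denominator degrees of freedom, the true type I error of a nominal 5% test is close to 0.05^(1/R).

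| c | R | True type I error |
|---|---|---|
| 0 | 1.00 | 5.0% |
| 0.005 | 1.13 | 7.1% |
| 0.01 | 1.26 | 9.3% |
| 0.02 | 1.52 | 13.9% |
| 0.03 | 1.78 | 18.6% |
| 0.05 | 2.30 | 27.2% |

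Simulating the stated ANOVA on the same assumptions gives about 5%, 7%, 9%, 14%, 18% and 27%, so the approximation holds.

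**Sensitivity.** A second simulation added a stable class ICC of 0.02 to 0.05 and made 60% of the remaining variance stable within the pupil. The group-by-time error was then about 10%, 16%, 22% and 31% at c = 0.01, 0.02, 0.03 and 0.05.

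**Stable class differences only.** With c = 0 and a stable class ICC of 0.05, the class effect cancels from the interaction and the error stays at 5%. It does not cancel from the group main effect. Averaged over three times, pupil variance within a class is 0.45 + 0.5/3 = 0.617. The inflation is (0.617 + 14 × 0.05) / (0.617 + 0.05) = 1.317 / 0.667 = 1.97. The true error is 2 × (1 − Φ(1.96/√1.97)), about 16%.

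**Comparison of arms at one time point** (for example, to follow up a significant interaction). The design effect is 1 + 13 × ICC, that is 1.26, 1.65 and 2.30 at ICC 0.02, 0.05 and 0.10. The error 2 × (1 − Φ(1.96/√DE)) is 8%, 13% and 20%.

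**Class as the unit.** The same ANOVA run on class means gave a simulated group-by-time error of about 5% in every setting. The inflation therefore comes from the choice of error term.

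**The case against.** The analysis gets two sentences in a condensed article, and the word used before the two factors does not formally close the list. A full protocol or SAP could add class, and mixed-model could loosely mean random class effects. The article also calls the testing preliminary and leaves its outcomes to be co-designed. On size, the natural test of the programme is group-by-time, from which stable class differences cancel. Only the class-by-time share then matters, and no document gives it. The main-effect and single-time rates concern tests that the article does not single out, and the class size is borrowed from the pilot.

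The points on size stand: the inflation is conditional and the figures are a range under assumptions. The point on wording does not remove the mismatch. The article did not leave the model open. It named one and listed terms that, read in the ordinary way, do not fit its own unit of allocation. If class effects are intended, one sentence would say so. A preliminary aim does not make standard errors valid in a 600-pupil controlled comparison.

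**Conclusion.** The concern holds. The article states a pupil-level analysis for a class-randomised comparison. The interaction test keeps its 5% level only if all classes would follow the same course over time apart from the programme. That is hard to defend over a 6-month class-based intervention and a 3-month follow-up. A class-by-time share of 1% roughly doubles the false-positive rate to 9 to 10%, and shares of 2 to 5% raise it to about 14 to 31% across the two sets of assumptions. These rates assume 15 classes per arm and 14 completers per class. Larger classes would make them worse. The existence of the mismatch depends on none of these figures. It should be corrected before the USE stage starts.

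**What to change.** In Data Analysis, replace the two-factor ANOVA with a linear mixed model:
- fixed effects for group, time and group-by-time, and for school where several classes come from one school (plus any stratification factor, if allocation is stratified);
- random effects for class and for class-by-time (or class-level random slopes);
- repeated measures within pupil;
- Satterthwaite or Kenward-Roger degrees of freedom, because the number of classes is likely to be small (about 30 on the pilot class size).

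Report the class ICC with the results. If a simpler analysis is preferred, the same ANOVA on class means, with degrees of freedom based on the number of classes, also restores the nominal level.

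The cost is a rewritten paragraph and a class identifier (and school identifier) recorded for every pupil. Confidence intervals will be wider, and precision will depend on the number of classes as well as the number of pupils, so the sufficiency statement under Participants should be checked against the new model.

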### Ethical Considerations

Institutional ethics approval has been requested and will be obtained for the SMARTS project. All participants will provide active, informed consent before their participation. For the participating children and young people, informed consent will also be obtained from a parent or legal guardian. The informed consent forms and participant information sheets are currently also under review by the institutional ethics board. Given the sensitive nature of the topic, the information sheets will include contact details from the researcher as well as several currently available mental health resources, should the participants feel the need for support following their participation in the study. All data collected throughout the project will be pseudonymized and stored for a duration of 10 years within a secure data repository following the completion of the project.

## Results

Funding for the SMARTS project was approved in January 2023. Upon obtaining ethics approval, participant recruitment for the first research phase will commence in September 2023. The full project will be completed by March 2027.

## Discussion

Children and young people living within urban environments form a particularly at-risk population for mental health problems [2]. School-based mental health programs have, therefore, often been proposed as key interventions to target this population [19-21]. Additionally, sports have also been proposed as a context for mental health promotion programs, as well as a “hook” to attract children and young people to such programs [32]. Nevertheless, there currently exists a “science-to-practice gap” in the implementation of mental health promotion programs for children and young people [18], with existing interventions often proving difficult to sustain and upscale to broader settings. One potential solution to this issue might lie in the use of participatory design approaches, focusing on the active involvement of intervention end users (ie, children and young people) as co-designers throughout all phases of intervention development. The SMARTS project, thus, aims to develop an intervention that is evidence-informed and, at the same time, engaging for children and young people, through the adoption of a rigorous participatory design approach [35].

To achieve this objective, the SMARTS project will co-design and evaluate a comprehensive evidence-informed school-based mental health promotion program, integrating sport sessions with class-based sessions, complemented with educational modules for teachers and parents. This intervention is targeted at school-going children and young people aged 13-15 years. This particular age range was chosen as it coincides with the typical age during which children and young people are at risk for first onset of psychological symptoms and distress [1]. The mental health promotion program will integrate principles based on MHL [39], psychological resilience [41], existing school-based programs to prevent psychological symptoms [23], and insights from the sport-for-development literature [45]. To develop the program, the rigorous participatory design framework presented by Hagen et al [35] will be adopted. Through several consecutive research stages, the SMARTS project will (1) co-design the multicomponent program, (2) explore how the intervention can be implemented most effectively within the Brussels school system, and (3) conduct preliminary process and outcome testing of the full mental health promotion program. A key challenge when conducting such a participatory design project lies in the recruitment and activation of all relevant stakeholders within the co-design process. However, this can be mitigated as the SMARTS consortium, which includes local school organizations, will play an active role in both participant recruitment and the design and implementation of the eventual organization.

With this intervention, we aim to provide a direct contribution to the promotion of children and young people’s mental health within the Brussels school context. This is particularly relevant as children and young people within the Brussels urban context tend to report higher prevalence rates of mental disorders, compared to regional or national averages [8]. In part, this may be attributed to increased mental health stigma, as well as experienced social and economic barriers toward traditional mental health care. At a broader level, we hope that conducting and documenting large participatory design projects like SMARTS can inspire and guide other researchers to tailor mental health interventions to specific at-risk populations.

## Appendix

Multimedia Appendix 1 Peer-review report from VUB Research (Brussels, Belgium).

## Abbreviations

MHL: mental health literacy
NSSI: nonsuicidal self-injury
SMARTS: Strengthening Mental Health and Resilience Through Schools
